### Sample size and power considerations

#### Power considerations for primary outcome

Twenty clusters will be randomized to each study arm, with the randomisation stratified by type of health facility. The sample size for this trial was calculated using the following assumptions, with testing carried out at the 2.5 % significance level for the primary endpoint to allow for multiple testing:

For the mean DD symptom severity score at 3 months.

The within-cluster standard deviation in both arms for the DD combined symptom severity score will be at most 4.4 units (based on the results of the INDEPTH trial in Uganda [43], for screen positive subjects).The mean symptom severity score in the CSC arm at 3 months will be 4 units compared to a mean score of 6 units in the EUC arm.The harmonic mean of the number of participants per clinic will be 15.The between cluster coefficient of variation for the PHQ-9 score will be 0.25 in both arms.

Using these assumptions and the formula from Hayes and Moulton [44] (page 110 Eq. 7.9) C = 1 + (zα/2 + zβ)2 {2 σw2 / m + k2 (µ02 + µ1 / (µ0−µ1) [44]; where *m* is the harmonic mean of the number of participants per clinic, *k* is the between cluster coefficient of variation, *σw*2 is the within-cluster variance of the DD combined symptom severity scores, *µ0* is the mean DD combined symptom severity score at 3 months in the EUC arm and *µ*1 the combined symptom severity score at 3 months in the CSC arm.

Then a sample size of 20 clusters per arm will give 90 % power to detect as statistically significant at the 2.5 % level a true mean difference between the EUC and CSC arms of 2 units in the DD symptom severity score.

The sample size calculation is conservative in having used a large estimate of the within cluster standard deviation, as adjusting for baseline DD score is likely to reduce this.

### Data collection and management

Data from study participants at baseline, 3 months, and 12 months’ post-enrollment will be collected on printed interviewer-administered face-to-face paper questionnaires which will be stored in lockable filing cabinets at each study site. All the completed questionnaires will be reviewed by a research team member for missing data and unusual responses. Corrective action will be undertaken where necessary by the study research assistant, either by means of a telephone call or by asking the study participant to come back to the clinic. For this, the Data Section of the MRC/UVRI & LSHTM Uganda Research Unit will design a study database in OpenClinica, using unique study identification-number as a linking field. At regular intervals study questionnaires will be retrieved and transferred to the data section of the MRC/UVRI & LSHTM Uganda Research Unit for double data entry. During data entry, the data manager will periodically carry out a set of pre-defined quality checks on the data and raise any queries with the research assistants through the study coordinator. The OpenClinica database will maintain a complete audit trail of the changes made during data cleaning. Once data for a given survey round in the cluster randomised trial has been cleaned and validated, the data will be locked and exported to Stata for statistical analysis. The dedicated data manager assigned to the study will carry out regular quality control checks on the study database. When all of the queries of a given phase of the study, or a given round of the cluster randomized trial have been addressed, the data manager will upload the cleaned data into the main study database. The main study database will be backed up onto a secure location using a mirror server. In addition, the data manager will maintain a password protected copy of the database on his/her computer and on an external hard drive. A detailed data dictionary will be prepared to help with the curation of the data. The master database for the study will be maintained on the server of the Unit. The data manager and study statisticians will also have password protected copies of the master database.

### Statistical analysis

Analyses will be conducted on an intention-to-treat (ITT) basis. For the primary outcome of ‘DD symptom severity scores at 3 months’ linear mixed models will be fitted to compare the two treatment arms (CSC and EUC) with terms for treatment arm, stratum (level of health facility) and baseline DD symptom severity score, with a random effect fitted for clinic. *A priori* moderators will include gender, social class and baseline severity.

For the binary secondary outcome measures, random effects logistic regression models will be fitted with similar terms to those fitted for the DD severity score analysis. Models with multiple time periods will be estimated using ANCOVA assuming low auto-correlation between time periods [45]. Exploratory longitudinal analyses will be carried out using three-level multilevel models with the levels being clusters, PLWH within clusters and occasions within PLWH (periods). These models will consider (a) the effect of period e.g. whether the symptom score decreases linearly over time and (b) whether there is a treatment arm by period interaction i.e. whether the treatment effect reduces or increases over time.

For the cost-effectiveness component of the study, a micro-costing will be performed to obtain the mean cost per patient, the EQ-5D will be used to construct QALYs and a Markov model will be used to predict the outcomes and cost over the lifetime of the patients [45].

Missing data on outcomes and key covariates will be assessed, and if > 5 % of participants are missing data multiple imputation methods appropriate for multilevel data will be used [46].

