### Participant eligibility criteria and recruitment

#### Inclusion criteria

PLWH who have been on ART for at least 6 months, ≥ 18 years, residing in the study area, medically stable (not too ill to require emergency admission) at the time of the study, conversant in English or Luganda (the predominantly used local language), willing to be home visited (in instances of loss to follow up) and able to give informed consent will be eligible for enrollment if they score ≥ 10 on the PHQ-9.

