### Study outcomes measures

The study outcome measures will be collected by means of questionnaires that will be administered to study participants by trained research assistants (TRA) who will be separate from the study implementation team. Data collection by TRA will be supported and overseen by Research Supervisors (RS; trained psychiatric nurses or psychiatric clinical officers who will each oversee four study PHCFs). The three-month outcome is the primary end-point of the trial as majority of study participants will have completed their BA sessions and we would expect the optimal effect of the treatment. The 12-month end-point is included to evaluate the sustainability of the effect of the intervention. The outcome assessment measures with the specific outcomes are summarised in Table 1. The primary outcome measure in this study will be the mean DD symptom severity scores (assessed using the PHQ-9) at 3 months.

**Table 1 Tab1:** HIV + D outcome measures and specific outcomes

Outcome	Source of data	Endpoint	
		Collected at 3 months	Collected at 12 months
Primary outcome			
Mean DD symptom severity scores	PHQ-9 [41]	√	
Secondary outcomes			
Mean DD symptom severity scores	PHQ-9 [41]		√
Remission (proportion with PHQ-9 scores < 5)	PHQ-9 [41]	√	√
Mean generalised anxiety disorder (GAD) severity scores	GAD-7 [47]	√	√
Quality adjusted life years (QALYs)	EQ-5D-5 L [48]	√	√
Days out of work (over 3 months)	Patient cost questionnaire	√	√
Functional impairment and welfare	OxCAP-MH [49]	√	√
Patients’ satisfaction with depression care	Modified Patient Satisfaction Survey by Ede et al. [50]	√	
Carers’ perceptions and satisfaction levels with integration efforts at HIV clinic	Modified Staff Survey by Ede et al. [50]	√	
Proportion with virological failure (a proxy measure of adherence; defined as a viral load of 400 copies/ml or more)	HIV viral load (copies/ml)		√
Reported adherence to ART (proportion of participants who have missed at least one dose of ART in the past three days compared against the baseline value)	Assessed by means of the question, *‘Have you missed taking ART in the last 3 days?’* Possible responses 1 = Yes, 2 = No	√	√

Key: Carer = lay health worker, case manager, mental health workers;* ART * antiretroviral therapy

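### If baseline is an occasion in the exploratory longitudinal models, as checking a linear decline requires, the arm-by-period interaction does not test whether the treatment effect changes after 3 months

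*Protocol article*

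**What the plan says.** All references are to the protocol article; the statistical analysis plan is not at hand.

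- Statistical analysis: "Exploratory longitudinal analyses will be carried out using three-level multilevel models". The structure is "three-level multilevel models with the levels being clusters, PLWH within clusters and occasions within PLWH (periods"). The visits that count as occasions are not listed.
- The same models are asked two questions. Question (b) is about the interaction: "whether there is a treatment arm by period interaction i.e. whether the treatment effect reduces or increases over time". Question (a), listed ahead of it, is about the time course: "the effect of period e.g. whether the symptom score decreases linearly over time".
- The sentence just before reads: "Models with multiple time periods will be estimated using ANCOVA assuming low auto-correlation between time periods".
- Data collection and management: "Data from study participants at baseline, 3 months, and 12 months’ post-enrollment will be collected".
- Study outcomes measures: "The 12-month end-point is included to evaluate the sustainability of the effect of the intervention". Table 1 there lists the 12-month mean PHQ-9 score as a secondary outcome.
- Inclusion criteria, the same in both arms: participants "able to give informed consent will be eligible for enrollment if they score ≥ 10 on the PHQ-9".

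**The concern.** The two questions put to these models need different sets of occasions. Two points always lie on a straight line, so question (a) can be checked only if baseline is one of three occasions. At baseline no treatment has been given and both arms enter under the same PHQ-9 threshold, so the expected arm difference is zero. Any later effect, however stable, is then a change in the arm difference over the modelled period. The interaction in (b) responds to the effect appearing between 0 and 3 months, whereas its stated meaning concerns the effect shrinking or growing once present.

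At stake is how durability is described. This interaction is the only analysis in the article that addresses change in the effect between visits. On the baseline-included reading, a durable effect could be reported as changing, and a fading one as growing or as unchanged.

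**Working it through.** **Inputs from the article (Sample size and power considerations):** 20 clinics per arm; harmonic mean 15 per clinic (300 per arm), or 30 per clinic at the full 1200 (600 per arm); within-clinic SD 4.4; between-clinic coefficient of variation 0.25; 3-month means 4 and 6, a difference of -2. Visits at 0, 3 and 12 months.

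**Assumptions not in the article:** within-person correlation 0.2 to 0.7; clinic SD 1.25 (0.25 x 5, the midpoint of 4 and 6), with half its variance changing by visit where stated; two-sided 5% level for this exploratory test; no dropout.

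**Step 1, the plan's own figure.** C = 1 + (z_a/2 + z_b)^2 x {2 x SD^2/m + k^2 (mu0^2 + mu1^2)}/(mu0 - mu1)^2. Here 2 x 19.36/15 = 2.581, and 0.0625 x (36 + 16) = 3.25. The sum is 5.831, and divided by 4 it is 1.458. With z values 2.241 and 1.282 at the 2.5% level, C = 1 + 12.41 x 1.458 = 19.09, so 20 per arm; power at 20 is 91.4%. The stated design reproduces. No figure is stated for the interaction.

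**Step 2, expected linear interaction with baseline as an occasion.** Months 0, 3, 12 have mean 5, so the centred values are -5, -2, 7 and the sum of squares is 25 + 4 + 49 = 78. With arm differences d0 = 0, d3 and d12, the interaction is (-2 x d3 + 7 x d12)/78. In balanced data this is also the random-intercept estimate.

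| Arm differences at 0, 3, 12 months | Interaction per month |
|---|---|
| Sustained (0, -2, -2) | (4 - 14)/78 = -0.128 |
| Halved (0, -2, -1) | (4 - 7)/78 = -0.038 |
| Down to 2/7 (0, -2, -4/7) | (4 - 4)/78 = 0 |
| Lost (0, -2, 0) | 4/78 = +0.051 |

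Negative means a growing benefit. If period is coded 0, 1, 2 instead, the interaction is (d12 - d0)/2: -1.0 per period if sustained, -0.5 if halved and 0 if entirely lost.

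**Step 3, how often it would be flagged.**

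- Random intercepts only, normal approximation: variance = 2 x 19.36 x (1 - r)/(n x 78). For r = 0.2 and n = 300 this is 30.976/23400 = 0.00132, SE 0.0364, z = 0.128/0.0364 = 3.52, rejection 94%. Across r = 0.2, 0.5, 0.7 and n = 300, 600, the sustained effect is flagged in 94-100%. The halved effect is flagged in 19-69%, below half in five of the six settings.
- Simulation, 4,000 trials per setting, r = 0.2 or 0.5, 15 or 30 per clinic, clinic-by-visit variation present, t-test on clinic-level slopes over 0, 3 and 12 months: sustained 75-92%; halved 12-17%; down to 2/7, 4.6-5.6%; lost 17-25%.
- The same with period coded 0, 1, 2: sustained 91-98%; halved 37-55%; lost 4.7-5.1%.
- Categorical period, joint 2-df test (noncentral chi-square, r = 0.2 or 0.5): sustained 94-100%.

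**Step 4, baseline not an occasion.** With only 3 and 12 months, a sustained effect gives an interaction of exactly 0 and simulated rejection of 4.7-5.5%. A halved effect is detected in 38-55% and a lost effect in 90-99%. Question (b) is then answered as described, but two points cannot show whether the decline is linear.

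**The case against.** The strongest reply is that the article never says baseline is an occasion. That is inferred from a linear decrease offered only as an example, and the preceding ANCOVA sentence points the other way: it normally means baseline as a covariate, with 3 and 12 months as the periods. On that reading the interaction does what is claimed. The text also speaks of models in the plural, so (a) and (b) need not come from one fit. Listing occasions and coding time are often left to the analysis plan, and the analysis is labelled exploratory.

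Most of this stands, and it makes the point conditional. It does not remove it, because the article puts both questions to the same set of models, and the reading that (a) needs makes the stated meaning of (b) wrong.

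Three stronger readings are tempting, and the article does not support them.

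- A reader might infer that the interaction simply tests for no treatment effect. That is exact only for the categorical joint test with baseline included. The linear null also holds for a real effect that fades to 2/7 of its 3-month size.
- A reader might infer that sustainability cannot be judged at all. Table 1 makes the 12-month PHQ-9 mean a secondary outcome. A categorical fit with baseline also yields the 12-minus-3-month difference if someone asks for it.
- A reader might infer that naming three levels commits the trial to one constant clinic effect and so to inflated error. Naming levels does not exclude a clinic-by-visit term, so this is not an error in the text.

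**Conclusion.** The point holds in conditional form. The article leaves open whether baseline is an occasion. If it is, the arm-by-period interaction does not isolate change in the effect after 3 months: a fully sustained 2-unit effect would usually be flagged (about 75-100%), a halved effect keeps the sign of a growing one though it is usually non-significant, and substantial fading can sit exactly on the linear null. If baseline is only a covariate, (b) is sound and linearity in (a) cannot be checked.

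The expected coefficients follow from the visit times and the assumed arm differences alone. The 3-month difference of 2 is the article's; the 12-month values are scenarios. The rejection rates depend on the assumed correlations, clinic variation, 5% level and complete follow-up.

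The consequence is limited to an exploratory analysis and to how durability is worded. The primary 3-month analysis and the secondary 12-month PHQ-9 comparison are untouched.

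**What to change.** In Statistical analysis, or in the analysis plan if it is still open:

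- Define the change in effect as the arm-by-visit contrast, the 12-month effect minus the 3-month effect, and report it with its confidence interval.
- Estimate it from a model with the 3- and 12-month scores as outcomes, visit as a categorical factor, baseline PHQ-9 and stratum as covariates, and random effects for clinic and participant.
- Describe the course from baseline separately, by visit means in each arm, and drop the reference to a linear decrease.

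A clinic-by-visit random effect is an optional refinement; it widens the interval if clinics drift between visits.

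The cost is wording only, with no new data. Power to show a halved effect is modest (38-55% under the assumptions above), so the interval should carry the interpretation, and a non-significant contrast should not be read as proof that the effect is sustained.

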### Monitoring the trial

Four committees will monitor the progress of the trial, that is, Independent Data Monitoring Committee (IDMC), Trial Steering Committee (TSC), Trial Management Team (TMT) and the Trial Management Group (TMG) and details are shown in Additional file 2: Appendix 2.

### Ethics and dissemination

The protocol was reviewed and approved by the Uganda Virus Research Institute (UVRI) Research and Ethics Committee (reference number GC/127/20/04/772), the Uganda National Council for Science and Technology (reference number HS645ES), and the London School of Hygiene and Tropical Medicine (LSHTM) Ethics Committee (reference number 22,567). Any protocol modifications will be submitted to the UVRI Research and Ethics Committee for review, and participants will be informed if warranted. The LSHTM is the trial sponsor. Written (or witnessed if the participant is illiterate) informed consent will be mandatory to enrolment. All participant data will be stored securely and access will be restricted. In order to maintain participant confidentiality, all study data collection forms will only be identified by the study identification numbers. Documents that contain participant’s names such informed consent forms will be stored separately from data collection forms. All databases will be password protected. HIV-infected persons who do not enrol in the study for any reason will be counselled and referred for care. Serious Adverse Events (SAEs) (death, suicide attempt, hospitalisation) from any cause will be reported as soon as possible within seven calendar days of becoming aware of SAE to the UVRI Research and Ethics Committee and to the IDMC.

Results produced by this investigation will be presented at local and international conferences and published in a timely fashion, ideally in the last year of the study period. All final peer-reviewed manuscripts that arise from this proposal will be submitted to the digital archive PubMed Central for open access.

## Discussion

The aim of the HIV + D trial is to provide evidence on the effectiveness and cost-effectiveness of a scalable model for the integration of depression management in HIV care in public health facilities in low resourced settings such as those in Uganda. This intervention model aims to reduce the treatment gap posed by the growing burden of depression among adult persons living with HIV in settings where they currently have no mental health care and where there is an acute shortage of mental health professionals. This project is responding to the Ministry of Health which for the first time in 30 years of the HIV epidemic in Uganda has called for the management of depression in the national HIV prevention and treatment guidelines [15]. These guidelines specifically called for an integrative approach to the management of HIV related comorbidities such as depression [15]. The HIV + D Trial is testing the effectiveness of a health systems intervention based on the MANAS intervention that demonstrated effectiveness for the management of depressive and anxiety disorders in primary care settings in India [30]. A variation of this model, the CobALT trial is currently underway in South Africa [37]. The collaborative care model being evaluated in this trial will be led by lay health care workers under the supervision of HIV care counsellors (general nurses trained in HIV counselling) and supported by mental health workers using a manualised behavioural activation based therapy (the Health Activity Program). The trial design is a cluster randomised trial conducted in 40 HIV care clinics in public health care facilities across three districts in central and south-western Uganda. The study outcomes will be measured on 1200 adult persons living with HIV who have screened positive for depression. It will provide evidence of the effectiveness and cost effectiveness of the intervention on mental, physical and health system outcomes and will highlight the benefits of attending to mental disorders in HIV care programming. Dissemination activities will be organised to share the findings from the cluster randomised trial with stakeholders. An application for further funding will be made to scale up the model if found to be effective.

## Data Availability

Data sharing is not applicable to this protocol as no datasets are generated or analysed yet.

## Abbreviations

ART: Antiretroviral therapy
BA: Behavioural Activation
LHW: Lay health worker
CobALT trial: Acronym for the trial, ‘Collaborative care for the detection and management of depression among adults receiving antiretroviral therapy in South Africa’
CSC Arm: Collaborative Stepped Care arm
DD: Depressive Disorders
EQ-5D-5 L: The EuroQol 5 dimensions
EUC Arm: Enhanced Usual Care arm
HIV + D: Acronym for the project, ‘Integrating the management of depression into routine HIV care in Uganda’
HIV + D Model: HIV + D Interventional model
LMIC: Low and middle income countries
MANAS: Acronym for the cluster randomised trial that was implemented in India to evaluate a stepped care collaborative delivery model for depression and anxiety disorders in primary health care
mhGAP: WHO’s Mental Health Gap Action Programme
WHO: World Health Organisation
MOH: Ministry of Health
MRC/UVRI & LSHTM Uganda Research Unit: Medical Research Council / Uganda Virus Research Unit & London School of Hygiene and Tropical Medicine Uganda Research Unit
OxCAP-MH: Oxford Capabilities Questionnaire for Mental Health
PHCF: Public health care facilities
PHQ-9: The Patient Health Questionnaire-9
PLWH: People Living with HIV
ToC: Theory of Change
UNCST: Uganda National Council for Science and Technology
UVRI: Uganda Virus Research Institute
REC: Research Ethics Committee
HIV/AIDS: Human immunodeficiency virus and acquired immune deficiency syndrome
